Homeopathic medicines are generally regarded as very safe, due to the low concentrations of active ingredients present, with adverse event rates generally estimated to be 3% or less and serious adverse events extremely rare (11, 14). In the United States, homeopathic medicines are regulated by the FDA under the 1938 Food, Drugs, and Cosmetics Act (15). The majority of homeopathic medicines are available OTC without a prescription required. According to the manufacturer (Boiron) of the product to be used in this study (Acidil), there have been no adverse event reports for this supplement over the last 10 years in the United States.

Despite the relative safety of homeopathic medicines, certain types of treatment reactions are commonly recognized by the homeopathic community. These include aggravations and provings. An aggravation is a transient aggravation of a patient's symptoms followed by a marked improvement in symptoms and is felt to be a positive prognostic sign of healing. A proving occurs when a patient manifests symptoms that the homeopathic medicine is designed to treat and usually occurs when a patient has received too much of the medicine and/or the medicine is poorly matched to the patient's symptoms. Aggravations and provings may explain the dynamic oscillations seen in patients' symptoms in the homeopathy arms, but not the placebo arms, of some randomized controlled trials (16, 17). These observations complicate the interpretation of treatment outcomes and may account for some inconsistent results in prior homeopathic studies. Thus, in our study, we propose to monitor dynamic changes in symptoms over time as well as conduct endpoint analyses.

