### B3. DESCRIPTION OF RESEARCH PROTOCOL

#### A. Study Design – Overview, Methods, Procedures

##### Overview

We propose to conduct a single-center, pilot feasibility, 2x2 factorial design randomized controlled trial assessing the effect of a homeopathic supplement (Acidil) and components of the placebo response (doctor-patient interaction and beliefs/expectations) on symptoms and HRQL in patients with GERD over a 2 week time interval. The Acidil vs. placebo intervention will be double-blinded and the standard vs. expanded interview intervention (doctor-patient interaction) will be single-blinded. Randomization will be by permuted block randomization with block sizes of 4 and 8. We plan to enroll 6 patients into each group for a total of 24 subjects in the study according to the adjacent scheme. Subjects will be evaluated in the GCRC at BIDMC at two timepoints: baseline and at 2 week follow-up.

|                    | Acidil  | Placebo |
|--------------------|---------|---------|
| Standard Interview | Group 1 | Group 2 |
| Expanded Interview | Group 3 | Group 4 |

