## **B. Statistical Considerations**

### **Sample Size Justification:**

We will screen a sufficient number of subjects to consent/enroll 24 subjects total into the study, 6 subjects in each of the 4 groups. This number was determined to ensure that we can complete enrollment within a 6-12 month time frame to assess study feasibility as our primary outcome.

As this is a pilot feasibility study, we do not anticipate having adequate power to show significant differences in treatment effects between groups, but do hope to generate estimates of effect sizes and demonstrate trends. Our chief secondary outcome will be the percent of subjects with 50% or greater improvement in heartburn symptom severity for the last 7 days of the study compared to baseline (compare groups 1+3 vs. groups 2+4 [Aim 2a] and groups 1+2 vs. groups 3+4 [Aim 3a]). We will also assess the percent of subjects with dynamic changes in heartburn symptom severity during the study period compared to baseline (compare groups 1+3 vs. groups 2+4 [Aim 2b]).

Table 2 illustrates power estimates using the Fisher exact test for between group differences ranging from 0.25 – 0.4 for an alpha of 0.05 and sample sizes of 24 subjects and 20 subjects per group (combining groups 1+3 and 2+4 or groups 1+2 and 3+4 for all analyses). We anticipate that we will have 30-50% power to detect a difference between groups. These power calculations are based on the assumption of no interaction effect.

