### Data Analysis:

All study data will be transcribed from paper surveys and entered into a REDCap database for data management. We will perform random screening of entered data to ensure accuracy. At the time that the REDCap database is translated into a SAS database for data analysis, the 2 main intervention codes (i.e., Acidil vs. placebo and standard vs. expanded interview) will be recoded by a member of the study team who did not have any subject contact ([name]) so that the principle data analyzer ([name]) is blinded to all study group assignments during the data analysis process. Initial analysis will include descriptive statistics assessing the baseline demographics, GERD and dyspepsia symptom frequency and severity, and HRQL among subjects in each of the 4 groups. All analyses described below will be intent-to-treat analyses and include an interaction term to account for possible interaction of the 2 main interventions in this study. The SAS database will not include any PHI and will be stored on the study investigator's H drive and thus will be password protected and behind a secure firewall.

**Hypothesis 1:** This study design will be both safe and feasible and subject recruitment will not be difficult.

Study safety will be established if there are no major adverse events attributed to Acidil and no statistically significant increase in minor adverse events between the Acidil and placebo groups. Feasibility will be established if we can demonstrate recruitment and retention of >90% of subjects within the pre-specified 6-12 month time frame.

**Hypothesis 2a:** Compared to subjects receiving placebo, more subjects receiving Acidil will experience a 50% or greater improvement in GERD symptom severity during the last 7 days of the study compared to baseline.

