A common measure for assessing treatment efficacy in GERD trials is assessment of the percent of subjects with a 50% or greater improvement in heartburn symptom severity (based on summation of symptom scores over time) using daily symptom diaries. We will perform this assessment by combining responses to the daytime heartburn, nighttime heartburn, and acid regurgitation questions on the daily symptom diaries for the last 7 days of the study compared to baseline. We will compare groups 1 and 3 with groups 2 and 4 using a logistic regression analysis and including an interaction term for the two study interventions. If there is no difference between groups, we will perform a secondary analysis using the GERD symptom severity score as a continuous variable to evaluate for potential trends.

**Hypothesis 2b:** The dynamic trajectory of symptom changes over time will differ between the Acidil and placebo groups. These differences may manifest as oscillations in symptoms in the Acidil group during the 2 week trial period, as well as changes in non-GERD and non-dyspeptic symptoms.

To assess for dynamic changes in treatment effects over time that may not be visible in end-point analyses such the one described in 2a above, we will perform a repeated measures analysis using generalized estimating equations and incorporating a time by treatment interaction term that will allow us to examine changes in GERD and dyspepsia symptom severity for the Acidil (groups 1+3) vs. placebo (group 2+4) group over the entire 2 week study period as well as look for differences in the number and frequency of non-GERD and non-dyspeptic symptoms based on data in the daily symptom diaries.

We will also assess the mean number of days without heartburn symptoms during the trial period for groups 1+3 and 2+4 as well as the mean number of days without dyspeptic symptoms during the

trial period (again groups 1+3 and 2+4) using the data from the GERD symptom diary.

**Hypothesis 2c:** Subjects receiving Acidil will report greater improvement in disease-specific and overall quality of life compared to the placebo group.

We will compare GERD-HRQL, Nepean Dyspepsia Index, and SF-12 scores between the Acidil and placebo groups (1+3 and 2+4), incorporating an interaction term for the two main treatment effects, using ANOVA.

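### Hypothesis 2b allows for symptom oscillations, but its analyses compare arm-level means or counts, where out-of-phase oscillations cancel, and the subject-level 2b outcome named under sample size is not carried through

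*Protocol*

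**What the plan says.** The Homeopathy background (B2) gives the motive for 2b: "Aggravations and provings may explain the dynamic oscillations seen in patients' symptoms in the homeopathy arms, but not the placebo arms". In Data Analysis, Hypothesis 2b is that symptom trajectories differ between Acidil and placebo, and the text adds: "These differences may manifest as oscillations in symptoms in the Acidil group during the 2 week trial period". It also allows for changes in symptoms that are neither GERD nor dyspepsia.

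The analysis set against this is: "we will perform a repeated measures analysis using generalized estimating equations and incorporating a time by treatment interaction term", applied to GERD and dyspepsia severity "for the Acidil (groups 1+3) vs. placebo (group 2+4) group over the entire 2 week study period". Two further comparisons follow: the number and frequency of other symptoms, and the mean number of days free of heartburn and of dyspepsia.

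The Sample Size Justification gives Aim 2b a different outcome: "We will also assess the percent of subjects with dynamic changes in heartburn symptom severity during the study period compared to baseline". That outcome is counted per subject. It does not reappear under Hypothesis 2b.

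**The concern.** The only time pattern of GERD and dyspeptic symptoms that the 2b text names is oscillation, which is a property of individual subjects' diaries. Every analysis listed under 2b works on arm-level means or counts. The GEE term asks whether the average curve differs between arms. Days without symptoms do not measure fluctuation either: five symptom-free days in one run and five scattered days give the same count.

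The trial is meant to yield preliminary effect sizes for a larger study. If oscillation occurs at different times in different subjects, the planned 2b analysis gives no estimate of it at any sample size, and a null result would say nothing about it. The two statistical sections also leave unclear which 2b outcome is intended.

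**Working it through.** **Plan's own figure.** None is given for the 2b model. Table 2 covers differences in proportions only. Its 18 entries reproduce within 0.016 with the continuity-corrected formula, but they have no bearing on the GEE.

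**Inputs from the Protocol.**
- Overview: "We plan to enroll 6 patients into each group for a total of 24 subjects in the study". Two cells of 6 make each 2b arm, so 12 vs 12, with 24 clusters.
- A daily diary over 2 weeks gives about 14 scores per subject.
- Data Analysis: all models "include an interaction term to account for possible interaction of the 2 main interventions in this study", so interview and drug-by-interview terms were included.
- Alpha 0.05, taken as two-sided.

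**Assumed, because the Protocol gives no values.** Variances, autocorrelation, and the period and size of the oscillation.

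**Step 1: cancellation.** Take a sinusoid as illustration. Let subject i's score on day t contain A·sin(2πt/P + φᵢ), with φᵢ differing at random between subjects.
- The expected value on every day is 0, so the arm mean gains no systematic pattern under any coding of time.
- What remains in a 12-subject mean is noise with SD (A/√2)/√12. For A = 1 this is 0.707/3.464 = 0.20.
- The within-subject variance rises by A²/2. With residual variance 1 and A = 1 it goes from 1 to 1.5, an SD of 1.22. With A = 1.5 it goes to 2.125, an SD of 1.46.

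The signal is therefore in each subject's variability and not in the arm mean.

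**Step 2: simulation, set-up 1.** Subject SD 1, within-subject SD 1 with AR(1) 0.4, 5-day period, exchangeable GEE with uncorrected sandwich variance and normal reference, 2,000 trials per scenario. The last column is a t test on log within-subject SD.

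| Scenario | Linear time-by-drug | Within-subject SD |
|---|---|---|
| No effect (slope SD 0 / 1) | 7.8% / 6.4% | 4.8% / 5.3% |
| Out of phase, amplitude 1 | 7.6% | 73.9% |
| Out of phase, amplitude 1.5 | 7.4% | 99.9% |
| Out of phase, amplitude 2 | 6.4% | 100% |
| In phase, amplitude 1 / 1.5 | 10.0% / 12.8% | 71.0% / 99.6% |

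**Step 3: simulation, set-up 2.** Random intercept SD 1, random slope SD 0.8, AR(1) 0.3, residual SD 1, independence working correlation. Out-of-phase oscillation of SD 0.5 / 0.75 / 1.0 gives linear GEE rejection of 7.7% / 7.3% / 7.2%, against 7.75% with no effect. A t test on log root mean square successive difference rejects in 23.6% / 71.9% / 98.7%.

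**Step 4: patterns locked to the start of treatment, set-up 2.** Shifts of ±0.75, small-sample-corrected GEE. The size and timing of the shifts are assumptions.
- Early worsening then improvement: GEE 45% (linear) or 64% (quadratic); successive differences 10%.
- Improvement then worsening: GEE 93% (linear); successive differences 9%.

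A separate run of these patterns gave 51-93% for the corrected GEE and 8-10% for successive differences. Each method sees what the other misses.

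**Step 5: size of the GEE test, if uncorrected.** In set-up 1 the sandwich standard error of the linear term averages about 0.95 of the true SD. Type I error is 6.4-7.8% for linear time (7.75% in set-up 2) and 9.2% for quadratic time in set-up 2. With a Mancl-DeRouen correction and a t reference, the linear term gives 3.5-4.4%.

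**The case against.** The strongest reply is that 2b is about differing trajectories, that oscillation is only one way the difference may show, and that a time-by-treatment term is the standard test of differing mean trajectories. Much of the Protocol's description is also tied to treatment onset. B2 describes transient worsening followed by improvement, B5 describes worsening after an initial gain, and all subjects start treatment at the first visit. This stands. It follows from Step 4 that successive differences would be a poor replacement for the GEE. It does not cover oscillation at differing times, and no common timing is stated.

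A second reply is that the Sample Size Justification already lists a subject-level 2b outcome, and that its definition may sit in an analysis plan not shown. The missing definition is therefore not held against the Protocol. The mismatch between its own two sections on what 2b comprises remains.

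Three stronger readings are tempting, and the document does not support them.
- **The GEE standard errors are too small.** The Protocol names no variance estimator, reference distribution or coding of time, so this is only conditional. An uncorrected 13-df test with day as a category does reject in about 72% of null trials, but nothing in the Protocol specifies that test.
- **A positive 2b result would more likely be noise than a real effect.** That needs a prior probability of effect, which is not available.
- **The 2b analysis has no power at all.** This is true for out-of-phase oscillation and untrue for onset-locked change.

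**Conclusion.** The point holds in limited form. As written, the 2b analyses can neither detect nor estimate oscillations that are out of phase between subjects; the GEE's rejection rate for them equals its false-positive rate. The cancellation follows from what the model estimates and does not depend on the assumed variances. The power of the per-subject alternative does depend on them: about 24% at oscillation SD 0.5, 72% at 0.75 and 99% at 1.0 in set-up 2. Those figures also assume unbounded normal scores, while the diary uses a 5-point scale.

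The consequence is modest. Feasibility is the primary outcome, 2b is secondary, and the trial disclaims adequate power. It is still worth correcting, because the aim is preliminary effect sizes, and the plan provides none for the pattern it singles out.

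**What to change.** - Keep the GEE as the 2b analysis of mean trajectory.
- Add, as a co-reported 2b analysis, a per-subject fluctuation measure of the daily GERD score, for example the within-subject SD or the root mean square successive difference. Compare groups 1+3 with 2+4 by linear model or permutation test, adjusted for the same measure in the baseline week.
- Make the Sample Size Justification and Hypothesis 2b name the same outcomes. Either carry the subject-level proportion into the 2b analysis or replace it there with the fluctuation measure.
- If the GEE is to use the usual sandwich variance with 24 subjects, state a small-sample correction with a t or F reference, and code time with few degrees of freedom.

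**Cost.** Wording, a little programming and one more secondary analysis; the diaries already hold the data. The baseline adjustment will be noisy, since 7 days give at most 6 successive differences against 13 over 14 days. On a 5-point scale variability can shrink near the floor as symptoms improve, so the measure should be read alongside the mean trend. The corrected trend test becomes slightly more conservative.

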#### Additional Exploratory Analyses:

1. Difference between the Acidil and placebo groups (1+3 and 2+4) and the standard vs. expanded interview groups (1+2 vs. 3+4) in the mean number of rescue antacid tablets required for symptom relief.
2. Difference between the Acidil and placebo groups (1+3 and 2+4) and the standard vs. expanded interview groups (1+2 vs. 3+4) in changes in dyspeptic symptoms during the last 7 days of the trial compared to baseline.
3. Difference between the Acidil and placebo groups (1+3 and 2+4) and the standard vs. expanded interview groups (1+2 vs. 3+4) in GSRS scores between the first and second study visits.
4. Difference between the Acidil and placebo groups (1+3 and 2+4) and the standard vs. expanded interview groups (1+2 vs. 3+4) in changes in non-GERD and non-dyspeptic symptoms during the last 7 days of the trial compared to baseline.
5. Changes in scores for symptom severity and well-being on the MYMOP questionnaire pre-post for the Acidil vs. placebo groups (1+3 and 2+4) and the standard vs. expanded interview groups (1+2 vs. 3+4).
6. Differences in GERD treatment satisfaction scores for the Acidil vs. placebo groups (1+3 and 2+4) and the standard vs. expanded interview groups (1+2 vs. 3+4).

7. Differences in scores on the CARE measure for the standard vs. expanded interview groups (1+2 vs. 3+4).
8. Changes in scores on the credibility questionnaire over time by treatment assignment.
9. Changes in medications during trial period for each group.
10. Percent of subjects in groups 3 and 4 whose symptoms match those for one of the homeopathic medicines in the combination homeopathic supplement based on either a clinical or classical homeopathic case analysis approach.

### C. Subject Selection

#### **Eligibility is defined by the following:**

##### **Inclusion criteria:**

1. Adult humans age 18-80.
2. Fluency in written and spoken English.
3. Heartburn symptoms 3 or more days per week for the past month.

##### **Exclusion criteria:**

- \*1. Subjects who have taken a proton pump inhibitor (PPI) or H2 receptor blocker within 2 weeks of the initial study visit.
2. Subjects with Crohns disease, systemic sclerosis, known active ulcer disease, gastric cancer, Barrett's esophagitis, significant pain or difficulty with swallowing, heavy alcohol use (defined by > 6 drinks/week for women and > 13 drinks/week for men), concurrent pregnancy (beyond first trimester as the physiology of heartburn symptoms in pregnant women is different from that in the non-pregnant population), dementia, or uncontrolled psychiatric disease.
3. Subjects unable to complete a paper symptom diary for 6 of 7 days prior to their baseline visit.
4. Subjects whose symptoms are predominantly dyspeptic more than heartburn or reflux.
5. Subjects who have used homeopathy for GI symptoms or have received constitutional homeopathic treatment within the past 2 weeks.
6. Subjects taking herbal products or other supplements for GERD or dyspepsia related symptoms (includes peppermint oil).
7. Subjects who have taken > 12 doses of NSAIDS within the prior 30 days (aspirin  $\leq$  325 mg daily is allowed).
8. Subjects with lactose intolerance. Our rationale: the Acidil and placebo tablets both contain lactose. Lactose intolerance is associated with GI symptoms, some of which overlap with symptoms that we are measuring in this study. Excluding lactose intolerant individuals will help make our data more interpretable.

\*If this population of subjects is too difficult to recruit, we will instead:

A) offer to enroll subjects if they wish to taper off their current medications. This will only be done if they do not have known Barrett's esophagus and are on a low dose PPI or H2 blocker. Subjects will be given standardized instructions for how to taper off of these medications using oral antacids as a bridge.

If we are unable to reach recruitment targets using secondary strategy A, we will also:

B) try to recruit subjects currently on stable drug therapy (no changes in PPI or H2 blocker dose x 2 weeks) with refractory GERD symptoms 3 or more days per week.

If we enroll subjects in groups A and/or B, we will modify our randomization approach to stratify by the different groups of subjects (i.e., based on status of PPI/H2 blocker use: none, recent, current) enrolled in the study so that they are equally distributed between arms.

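### If the recruitment fallback is used, randomisation is stratified by PPI/H2-blocker status but the continuous-outcome models omit that stratum, so their confidence intervals are too wide if it is prognostic

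*Protocol*

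**What the plan says.** The default design is unstratified: "Randomization will be by permuted block randomization with block sizes of 4 and 8", with the size given as "We plan to enroll 6 patients into each group for a total of 24 subjects in the study" (Protocol, Overview). Under Exclusion criteria, a starred note describes two successive fallbacks. Strategy A admits people tapering off a low-dose PPI or H2 blocker. Strategy B admits people with refractory symptoms on stable drug therapy. If either is used, "we will modify our randomization approach to stratify by the different groups of subjects", with strata "based on status of PPI/H2 blocker use: none, recent, current". The stated purpose is to spread these groups equally over the arms.

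The Data Analysis section fixes the terms of the between-arm models. Every analysis carries the interaction of the two interventions. For hypothesis 2a the text is "We will compare groups 1 and 3 with groups 2 and 4 using a logistic regression analysis and including an interaction term for the two" (the two being tablet and interview type). Should that show no effect, the severity score is analysed as a continuous variable. Hypothesis 3a is analogous. Hypothesis 2b uses generalised estimating equations with a time-by-treatment term. Hypotheses 2c and 3b compare the three quality-of-life scores "incorporating an interaction term for the two main treatment effects, using ANOVA". Neither these models nor the ten exploratory analyses mention the stratum.

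**The concern.** The Protocol changes the design conditionally without changing the analysis to match. By stratifying, the investigators treat drug status as something that could matter to outcome. If it does, a model without it leaves the between-stratum variance in the residual, although stratification has already removed most of that variance from the treatment contrast. The estimated standard error is then larger than the true one, and the interval is wider than the design earns.

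Effect-size estimates for planning a larger trial are one of the pilot's stated products, so the width of those intervals matters even though no test is expected to have adequate power.

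**Working it through.** **Inputs from the Protocol.** 24 subjects in four groups of 6, hence 12 per pooled arm; blocks of 4 and 8; up to three strata; model with two interventions and their interaction, leaving 24 − 4 = 20 residual degrees of freedom.

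**Assumptions.** The Protocol gives neither stratum sizes nor prognostic strength. I take strata of 12, 6 and 6 and let them explain a share R² of the outcome variance, with total variance 1 (apart from any treatment effect). Power figures assume a true difference of 1 SD.

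**The Protocol's own figures.** Table 2 concerns the responder endpoint only. It reproduces with a corrected arcsine approximation to Fisher's test (.25 v .5 at 24 per group: 0.325). It uses 24 and 20 per pooled arm, not 12, which is a separate matter. It contains no figure for the continuous outcomes.

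**Closed form, strata exactly balanced over arms.** The variance factor for the pooled contrast is 1/12 + 1/12 = 1/6.

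- Without the stratum, the expected residual mean square is [24·R² + 20·(1 − R²)]/20 = 1 + 0.2·R². Half-width ≈ 2.086 × √[(1 + 0.2·R²)/6].
- With the stratum (18 degrees of freedom), the residual variance is 1 − R². Half-width ≈ 2.101 × √[(1 − R²)/6].

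| R² | Without stratum | With stratum |
|---|---|---|
| 0 | 2.086 × √(1/6) = 0.852 | 2.101 × √(1/6) = 0.858 |
| 0.20 | 2.086 × √(1.04/6) = 0.868 | 2.101 × √(0.80/6) = 0.767 |
| 0.30 | 2.086 × √(1.06/6) = 0.877 | 2.101 × √(0.70/6) = 0.718 |

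**Simulation with real blocks.** Permuted blocks of 4 or 8 within strata, 20,000 trials per row, each pair given as without v with the stratum:

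| R² | Half-width (SD) | Coverage | Power |
|---|---|---|---|
| 0 | 0.85 v 0.86 | 95% v 95% | 64% v 62% |
| 0.20 | 0.87 v 0.77 | 97% v 95% | 63% v 72% |
| 0.30 | 0.87 v 0.72 | 98% v 95% | 63% v 77% |

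**Other layouts.** In units of the within-stratum SD, two strata of 14 and 10 differing by 0.5 SD give 0.880 v 0.854 (3% narrower with the stratum). Three strata of 8 with effects 0/0.5/1 SD give 0.926 v 0.851 (8% narrower), and with effects 0/1/2 SD give 1.135 v 0.852 (25% narrower). With no stratum effect, strata of 8/8/8 give 0.842 v 0.850.

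**Imbalance within strata.** Across several layouts, the chance that some stratum has an Acidil-placebo difference of 2 or more is 31-71%, with 12/6/6 at the top. Yet the spread of the point estimate hardly moves: at R² = 0.20 its standard deviation is 0.383 without and 0.377 with the stratum. The gain is a correctly sized interval, not removal of a material imbalance.

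**Responder endpoint.** In simulated logistic fits at 24 subjects, adding the stratum raised the mean standard error of the log odds ratio from 0.90 to 0.96 with no stratum effect, from 0.90 to 1.00 with stratum effects of ±0.75 on the log-odds scale, and from 0.88 to 1.08 with ±1.5. That is 0.96/0.90 = 1.07 up to 1.08/0.88 = 1.23, or 7-23% wider. Separated or non-estimable fits rose from 5-15% to 16-52%.

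**The case against.** The strongest reply is that this is doubly conditional and ordinarily left to the statistical analysis plan. A fallback must be opened, and drug status must then predict the outcome. All entrants have symptoms on at least 3 days a week, so its value for predicting change is not obvious. Feasibility is the primary outcome, and the error is conservative. Under hypothesis 3c the investigators also say the sample is too small for confounder adjustment.

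Most of this stands and limits the weight of the point; it does not remove it. The Protocol names model terms hypothesis by hypothesis, so a plan that followed it literally would omit the stratum. The 3c remark concerns confounders in a logistic model, which differs from carrying a randomisation factor in a linear one. Nothing in the Protocol forbids the stratum term, so this is a mismatch to close and not an exclusion to reverse.

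Three stronger readings are tempting and not supported:

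- **All intervals are too wide.** A reader might infer this for the chief efficacy endpoint too. For the logistic responder models the reverse holds: stratum terms widen the log-odds interval and often break the fit. They also change the target: in a check with 240 subjects and a true conditional log odds ratio of 1.0, the estimate was 0.72 without the stratum and 1.00 with it.
- **Small-block imbalance distorts the pooled contrasts.** Randomisation leaves them unbiased on average, and adjustment barely changes their spread.
- **The 2b analysis would gain.** Its target is the time-by-treatment term. A factor constant over time does little for that term, and with complete diaries and an identity link it does nothing.

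**Conclusion.** The point holds for the continuous between-arm analyses only: the ANOVAs of GERD-HRQL, Nepean and SF-12 scores under 2c and 3b, and the continuous severity score under 2a. If a fallback is used and drug status explains 20-30% of outcome variance, omitting it gives half-widths of about 0.86-0.88 SD where 0.72-0.77 SD would be valid, and coverage of 97-98% in place of 95%. Weaker strata bring a gain of only a few per cent, and non-prognostic strata bring none. Stratum sizes, variance shares and the 1 SD effect used for power are assumptions. The consequence is lost precision, not false-positive risk, so this is a modest but worthwhile correction.

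**What to change.** Add one sentence to the Data Analysis section: if fallback A and/or B is opened, the randomisation stratum (PPI/H2-blocker status: none, recent, current, as applicable) enters as a fixed factor in the ANOVAs for 2c and 3b and in the continuous severity analysis under 2a.

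The variable is needed for randomisation anyway. The cost is 1 residual degree of freedom with two strata or 2 with three, worth about 0.5-2 power points if the stratum is not prognostic.

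Leave the logistic models for 2a and 3a without stratum terms at this sample size. A stratified risk difference may be reported beside them as a supportive summary; it would not replace the model with the interaction term that the Protocol requires. No change to the 2b model is asked for on this ground.
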